## Abstract

**Background:**

New electronic health technologies are being rapidly developed to improve the delivery of mental health care for both health professionals and consumers and better support self-management of care. We developed a Web-based platform (the InnoWell Platform) that supports the prevention, early
intervention, treatment, and continuous monitoring of mental health and maintenance of well-being in people aged 2 years and older. The platform is a customizable digital tool kit
that operates through existing service providers who utilize the
system to provide their consumers with access to evidence-based
assessments and feedback, intervention options, and outcome
monitoring. It does this by collecting, storing, and reporting
personal and health information back to consumers and their
health professionals to promote collaborative care partnerships
that aim to improve the management of mental ill health and
maintenance of well-being

**Objective:**

The aim of this study was to describe the research protocol for a naturalistic prospective clinical trial wherein all consumers presenting for care to a traditional face-to-face or Web-based mental health service in which the InnoWell Platform is being offered as part of standard clinical care will be given the opportunity to use the platform.

**Methods:**

The Web-based platform is a configurable and customizable digital tool that assists in the assessment, monitoring and management of mental ill health, and maintenance of well-being. It does this by collecting, storing, and reporting health information back to the person and his or her clinician to enable transformation to person-centered care. The clinical trial will be conducted with individuals aged 2 years and older presenting to participating services for care, including persons from the veteran community, Aboriginal and Torres Strait Islander people, people from culturally and linguistically diverse backgrounds, the lesbian, gay, bisexual, transgender, and intersex community, and those from broader education and workforce sectors, as well as people with disabilities, lived experience of comorbidity, complex disorders, and suicidality.

**Results:**

Project Synergy was funded in June 2017, and data collection began in November 2018 at a youth mental health service. At the time of this publication, 5 additional services have also begun recruitment, including 4 youth mental health services and a veteran’s service. The first results are expected to be submitted in 2020 for publication.

**Conclusions:**

This clinical trial will promote access to comprehensive, high-quality mental health care to improve outcomes for consumers and health professionals. The data collected will be used to validate a clinical staging algorithm designed to match consumers with the right level of care and reduce the rate of suicidal thoughts and/or behaviors and suicide by suggesting pathways to care that are appropriate for the identified level of need, while simultaneously enabling a timely service response.

**Trial Registration:**

Australian New Zealand Clinical Trial Registry ACTRN12618001676202; https://www.anzctr.org.au/Trial/Registration/TrialReview.aspx?id=374632 (Archived by WebCite at http://www.webcitation.org/78TOi5jwl)

**International Registered Report Identifier (IRRID):**

DERR1-10.2196/13955

## Introduction

### Background

As we move further into the twenty-first century, major revolutions in technology are transforming the way we live our lives—from the way we socialize, work, access information, and receive services. The mental health sector, like many others, is undergoing immense change in the face of this revolution, whereby new technologies are being developed at a rapid pace, many of which challenge the way people receive and manage their health care [1]. This is evident in the dramatic increase in the number of mobile apps, internet-based resources, and platforms that target mental health problems [2]. Although it remains a major priority to develop and assess effective Web-based interventions, an equally important task is to determine how these technologies can effectively integrate with existing health services in ways that improve the delivery of mental health care for the service, consumers’ health professionals, and presenting consumers [3].

The Australian Federal Government initiated the National Mental Health Strategy in 1992 [4], promoted by 5-yearly government plans outlining priority areas for investment and reform [5-9]. Despite the efforts of the last 25 years, the most recent report from the National Mental Health Commission (NMHC) continues to highlight fundamental shortcomings within the mental health system, including persistent stigma, poor experiences of care by individuals with lived experience, families and support people, delays in service provision, fragmented services, and inefficient and ineffective use of resources [10]. The NMHC review emphasizes the key concepts of person-centered care, personalized care options, regionalization of mental health services and suicide prevention, adoption of new technologies, and systematic evaluation to drive future investments [11]. In relation to the latter, the Fifth National Mental Health and Suicide Prevention Plan now includes 24 national key performance indicators that can be reported on to track the progress of the plan [9], including prevalence of mental illness, changes in mental health consumers’ clinical outcomes, rates of employment and social, community, and family participation among individuals with mental illness, and rates of suicide. Technology is increasingly recognized as a way to support and drive mental health service reform. Electronic health (eHealth) is broadly defined by the World Health Organization as the use of information and communication technologies for health-related purposes, such as service delivery [12]. Various models of eHealth services have been shown to be successful, including stand-alone systems for symptom prevention and self-help, consumer-assisted care, such as peer support, virtual clinics offering professional care, and stepped-care systems for integrated care [13]. The Australian Government published its “E-mental health strategy for Australia” in 2012 to promote its broader mental health reform agenda, emphasizing the ability of eHealth apps, etools, and platforms to deliver evidence-based interventions on the Web as a complement to traditional face-to-face services to improve health outcomes [14]. Importantly, eHealth services can improve access to mental health care by overcoming issues of distance, cost, and stigma.

### Stage-Based Stepped Care

In addition to revolutions in technology to support service delivery, there have also been advances in service models that aim to match consumers to the right level of care (ie, right care, right time). Clinical staging models are commonly employed in medical settings for this purpose, and they have more recently been implemented in clinical psychiatry [15]. Staging models consider the spectrum of mental ill health, and they aim to place consumers on that continuum, from those with risk factors with symptoms or impairment through to those with persistent and recurrent syndromes [15]. The emphasis is then on matching consumers at various stages to interventions that are appropriate to that stage [16]. As highlighted in Textbox 1, a staged-based stepped-care model combines the principles of clinical staging with the objectives of stepped care, including the use of low-intensity interventions for those at early stages and offering more intensive interventions to consumers at higher stages, while monitoring outcomes to increase or decrease service intensity as needs change [3].

### Suicide Prevention

The Zero Suicide in Health Care International Declaration was developed collaboratively by international leaders in mental health and addiction services with the aim of making suicide a “never event” [17]. This global initiative includes crucial recommendations and targets to promote suicide prevention worldwide, including fostering a safety-oriented culture to reduce the rates of suicide for consumers under care, employing an evidence-based approach to enhancing routine care and driving system changes that will result in improved outcomes and better care for those identified as being at risk, investing in training for health professionals aimed at improving identification, assessment, and management of suicidal thoughts and/or behaviors and risk factors thereof (eg, chronic pain, substance misuse), and systematically identifying, assessing, and monitoring suicidality in the broad consumer base for a service for the purposes of triaging individuals to the appropriate intensity of care. The abovementioned goals are synonymous with the core principles of the InnoWell Platform, which include increasing access to standardized, broad-based assessment, identifying and tracking consumer needs, matching those needs with personalized care options without having to wait for an appointment, enhancing the quality of the care provided to consumers, and supporting and guiding health professionals at all levels of experience to foster skill and professional development. Furthermore, the platform’s suicide escalation protocol is specifically designed to facilitate the detection of suicidal thoughts and/or behaviors and suggest pathways to care that are appropriate for the identified level of need, while simultaneously enabling a timely response from health professionals for those consumers reporting high suicidality [18]. Suicide prevention was highlighted as one of the priority areas in the Fifth National Mental Health and Suicide Prevention Plan [9]. Government agencies, service providers, and community agencies have all been identified as being key to reducing suicide rates and improving health outcomes. Despite efforts to improve suicide prevention in Australia, there has been no reduction in suicide rates over the past decade [19].

Key features of stage-based stepped care.Provide broad and holistic initial screening, followed by more targeted mental health assessment for those who endorse screening questionsThe intensity of the intervention should be matched to the consumer’s level of need as determined by clinical stageProvide parallel interventions for risk factors associated with poor outcomes (eg, unemployment, alcohol, and/or other substance misuse)Employ proactive monitoring of treatment progress and outcomes

### The InnoWell Platform

Through a process of participatory design with lived experience, health professionals, and service staff (including administration and management), we have developed a Web-based platform (the InnoWell Platform) that supports the prevention, early intervention, treatment, and continuous monitoring of mental ill health and maintenance of well-being in people aged 2 years and older [20]. The platform is a customizable digital tool kit that operates through existing service providers who utilize the system to provide their consumers with access to evidence-based assessments and feedback, intervention options, and outcome monitoring. It does this by collecting, storing, and reporting personal and health information back to consumers and their health professionals to promote collaborative care partnerships that aim to improve the management of mental ill health and maintenance of well-being. This platform uses multiple sources of information to develop a comprehensive understanding of the consumers’ needs and track their progress over time. This primarily involves Web-based self-reported psychometric measures from both consumers and their health professionals, as well as objective behavioral data collected via third-party integrations. Textbox 2 highlights the functionality built into the InnoWell Platform.

Specifically, in relation to suicide prevention, the InnoWell Platform employs a suicide escalation protocol derived from previous work [18]. In the current platform, suicidal thoughts and/or behaviors are assessed using 2 self-report surveys: Suicidal Ideation Attributes Scale [21] and Columbia-Suicide Severity Rating Scale [22]. Suicidal ideation without plan or intent in the past month triggers a pop-up for the consumer in the platform, providing details for crisis support services. Self-report of suicidal ideation with a plan and/or intent and/or a suicide attempt within the past 3 months triggers both the pop-up for the consumer and sends a notification to the consumer’s health professional, requiring a clinical care action (eg, telephone contact, action safety plan).

### Primary Objective

The primary objective of this clinical trial (Australian New Zealand Clinical Trial Registry ACTRN12618001676202) is to validate the algorithms used to derive stage-based stepped care on data collected by the platform and previously published staging criteria [15]. To do this, 4 independent ratings of stage-based stepped care will be compared: (1) platform generated, (2) health professional, (3) multidisciplinary team via consensus, and (4) expert-clinician reference group (comprising 3 or more academic health professionals with “area of research expertise” in stage-based stepped care for mental ill health). This expert group will review the clinical data of a subset of randomly generated consumers and independently allocate clinical stage.

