#### Screening Procedures

It will be standard clinical care for all consumers presenting to a traditional face-to-face or Web-based mental health service utilizing the InnoWell Platform to be directed to the platform for assistance in assessment, management, and monitoring of their mental ill health and maintenance of well-being.

On contacting the service either by telephone (or short message service), on the Web (eg, email, chat), or in person, the consumer will be introduced to the clinical trial via an ethics-approved script. Although this script is generic and adaptable to different populations, settings, and services, it informs the consumer of what is involved in using the platform and notifies them that the data collected by the platform will be shared with their service provider to promote person-centered collaborative care and shared decision making. If the consumer is interested and responds “Yes,” they will receive a unique email invitation to sign up to the platform. When the participants receive the email invitation, they will be required to accept the invitation and be directed to “Sign up” by creating an account. If they do not sign up immediately, they will be sent a reminder via short message service. The participants will be required to review and accept both the “Privacy” and “Terms of use” within the platform before proceeding to a “Research data sharing” screen, which is where details about this clinical trial are contained.

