### The InnoWell Platform Description

The InnoWell Platform is being embedded within traditional face-to-face and Web-based mental health services, and it is being offered to consumers presenting to those services as part of standard clinical care. It is a Web-based platform, and it can be accessed via traditional computing and mobile devices. As outlined in Textbox 2, the platform allows consumers to complete Web-based clinical assessments to understand their needs; explore their personalized dashboard of results, including current symptoms, level of functioning, and health history (see Figure 1); select from recommended care options (eg, fact sheets, apps, etools, and other Web-based systems) to support their mental health and well-being (see Figure 2); track their progress (in real time); share their dashboard and plan with their health professional(s) to support care.

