Given the emphasis on suicide prevention, the InnoWell Platform has been built to include immediate access to crisis support options. At any time when engaging with the platform, a participant has access to the “I need help now” button (see Figure 3), which provides contact details for crisis services (eg, Lifeline, Beyond Blue, and Kids Helpline). As described previously, these support options also appear as a pop-up directly after the participant scores low, moderate, or high on the suicidal thoughts and/or behaviors health card. When a participant scores high on this health card, a notification of suicide risk is also triggered for the treating health professional requiring clinical action.

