### Outcomes

#### Primary Outcome

The platform-generated assignment of stage-based stepped care derived from an algorithm calculated from data collected by the platform will be compared with that allocated by the health professional working directly with the consumer, the within-service multidisciplinary consensus team, as well as by an independent expert-clinician reference group, all of which will rely on previous published clinical staging criteria [15]. For example, to meet criteria for Stage 2 or higher for depression, the disorder needs to have features indicative of more severe disorders, including psychomotor retardation, agitation, impaired cognitive function, severe circadian dysfunction, psychotic features, brief hypomanic periods, severe neurovegetative changes, or severe suicidality. Although a clinician will assess these features as part of standard clinical care to assign clinical stage, the platform will rely on the scores on several health cards (ie, depression, mania-like experiences, psychotic-like experiences, alcohol use, and eating behaviors and body image) for this purpose. The primary outcome will be the reliability of the ratings across these 4 methods of assigning clinical stage as assessed using Cohen kappa coefficient.

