## Discussion

### Person-Centered Care

At its core, the InnoWell Platform is designed to promote person-centered health care and assist clinical practices that place consumers as equal partners in health care decision making. The platform is also intended to help minimize the variability in care provision between health professionals and services by supporting clinical judgement with data. In addition, the platform aims to maximize the use of available resources and minimize duplication of services and wastage of time for all users, including consumers, health professionals, and service staff.

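### The stage ratings are called independent, but the described design does not secure this for the health-professional and team ratings, so their kappas with the platform may be inflated

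*Protocol article*

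**What the plan says.** The Primary Objective is to validate the staging algorithm, and for this "4 independent ratings of stage-based stepped care will be compared": platform, health professional, multidisciplinary team by consensus, and an expert-clinician reference group. The Primary Outcome is the "reliability of the ratings across these 4 methods of assigning clinical stage as assessed using Cohen kappa coefficient". Data Analysis rests scientific validity on the same agreement statistics.

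Elsewhere the article describes how the platform reaches the people who supply two of these ratings:

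- The InnoWell Platform: it works by "collecting, storing, and reporting personal and health information back to consumers and their health professionals".
- Textbox 2: allocating a clinical stage and suggesting a level of care are listed as built-in functions.
- Screening Procedures: consumers are told at first contact that "the data collected by the platform will be shared with their service provider".
- The InnoWell Platform Description: consumers can "share their dashboard and plan with their health professional(s) to support care".
- Participant Procedures: after a high suicidality score, "a notification of suicide risk is also triggered for the treating health professional requiring clinical action".
- Person-Centered Care (Discussion): the platform is intended to "minimize the variability in care provision between health professionals and services by supporting clinical judgement with data".

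The article does not say whether the professional or the team is masked to the platform's stage, or in what order the ratings are made. It describes the experts as independent and as working from clinical data, without saying whether those data include the platform's stage or scores.

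**The concern.** Kappa supports a validity claim only if each rater assigns a stage without knowing the other raters' answers. Here one rater is a tool that feeds information to two of the others and is built to inform their decisions. If a professional or a team has seen the platform's stage, platform-versus-clinician kappa partly measures how often the tool is followed, not whether its stage is right.

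The comparison affected is the primary one. More participants would not remove such a bias; they would only estimate the biased value more precisely. Nor can it be separated out later if nobody recorded which stage came first. The abstract reports data collection since November 2018, with five further services recruiting, so ratings without a recorded order may already be accumulating.

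**Working it through.** **Figure to reproduce.** There is none. The article gives no target kappa, expected agreement or sample size.

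**Step 1: can platform information reach raters 2 and 3 before they stage?** Consumers are invited to the platform when they contact the service (Screening Procedures), so platform results can exist before a clinician stages. Those results go to the service and the treating professional (sections cited above). One of them bears directly on staging: a high suicidality score triggers a notification to the treating professional, and the Primary Outcome section names severe suicidality among the features for Stage 2 or higher in depression. Exposure to platform information is thus part of the design. Exposure to the platform's stage is possible, because stage allocation is a listed function, but it is not stated.

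**Step 2: direction and possible size.** Assumptions, none of them from the document:

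- platform and clinician have the same stage distribution, with S = sum of squared stage proportions;
- kappa under blinded rating is k0;
- in a share c of cases, unrelated to case difficulty, the clinician takes over the platform's stage.

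Blinded rating gives observed agreement po = k0 + (1 − k0)S and chance agreement pe = S. With adoption, po becomes c + (1 − c)po and pe is unchanged, so

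observed kappa = [c + (1 − c)po − S] / (1 − S) = c + (1 − c)k0.

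Worked case with four equal stages, k0 = 0.40 and c = 0.3:

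- S = 0.25, and blinded po = 0.40 + 0.60 × 0.25 = 0.55;
- po with adoption = 0.3 + 0.7 × 0.55 = 0.685;
- kappa = (0.685 − 0.25) / 0.75 = 0.58, equal to 0.3 + 0.7 × 0.40.

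| Blinded kappa | c = 0 | c = 0.1 | c = 0.2 | c = 0.3 | c = 0.5 |
|---|---|---|---|---|---|
| 0.20 | 0.20 | 0.28 | 0.36 | 0.44 | 0.60 |
| 0.40 | 0.40 | 0.46 | 0.52 | 0.58 | 0.70 |
| 0.60 | 0.60 | 0.64 | 0.68 | 0.72 | 0.80 |

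Computing kappa from the full joint table gave the same values for four equal stages, four unequal stages (0.30, 0.45, 0.20, 0.05) and five equal stages.

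**Step 3: which comparisons are affected.** Platform versus professional and platform versus team are exposed. Platform versus experts is exposed only if the expert material shows the platform's stage, which the article does not say. It also does not say whether the treating professional sits on the consensus team, so the independence of that pair is open too.

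**The case against.** A reader might infer that clinicians stage with the platform's stage in front of them, so that the four ratings are not independent and agreement is inflated. The document does not support that, for these reasons:

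- No section says that a clinician sees the platform's stage before rating. The Primary Outcome section describes two routes: the clinician's own assessment of staging features in routine care, and the platform's use of health card scores. This stands.
- The dashboard is described in terms of symptoms, functioning, history and score levels, with no mention of a stage, and sharing it is something the consumer can do. Seeing a depression score is not the same as copying a stage, and raters in agreement studies often judge the same case material. This stands, and the formula above models only adoption of the stage.
- The statement on reducing variability is Discussion text about care provision, not about stage assignment. This stands as a limit on how much weight it carries.
- The experts are said to allocate stage independently. This stands, so a claim about all four ratings is too broad.
- The inflation figures depend on an assumed adoption share, and the article sets no kappa threshold that could be passed wrongly. This also stands.
- A condensed article may leave masking and rating order to the full protocol. That answers only part of the point. The article does more than omit a detail: it asserts independence as a property of the primary comparison while describing a workflow that can undo it. If the full protocol has masking, one sentence in the article settles the matter.

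**Conclusion.** The point holds in a limited form. Independence of the health-professional and team ratings from the platform is claimed but not secured by the design as described, so the platform-versus-professional and platform-versus-team kappas may be inflated. Any adoption of the platform's stage in cases that would otherwise have disagreed moves kappa upward. How far cannot be derived: the range of 0.46 to 0.70 for a blinded kappa of 0.40 rests on an assumed adoption share of 10% to 50%, equal stage distributions, and adoption unrelated to case difficulty. Without adoption this model gives no inflation. The finding does not extend to the expert ratings, beyond the need to state what the experts are shown.

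**What to change.** In the Primary Objective and Primary Outcome:

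1. Have the professional's stage and the team's consensus stage entered and time-stamped before the platform's stage is shown. Suicide notifications stay as they are.
2. Flag ratings made after the platform's stage was viewed. Leave them out of the main kappa, and report kappa with and without them.
3. Withhold the platform's stage and the other ratings from the expert case packs.

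Where this is not feasible, delete the word independent for the professional and team ratings, report their kappas with the platform as possibly inflated, and base the validation claim on platform versus masked experts. This fallback needs only a change of wording and masked expert packs; workflow at the services is untouched.

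Cost of the main option: a protocol clarification and a small workflow change in a tool already in routine use. Some ratings would drop out of the main comparison. If those made after viewing differ in kind from the rest, this selects the sample, which is why both kappas should be shown.
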